### Methods against bias

To randomly allocate influencing factors and to avoid selection bias, patients are randomly assigned by centralised randomisation to each group (intervention group and wait-list/TAU control group). An internet-based randomisation system (http://randomizer.at) is used. The randomisation is done in an allocation ratio of 1:1 with variable block length and is stratified for each participating centre.

To ensure that all participating centres will implement the SST and parent training in a very comparable way across centres, all therapists are trained in the SOSTA-FRA program before the beginning of the study in their centre. Further, all therapists are supplied with a detailed written manual including all performance rules. Regular telephone supervision and meetings are provided. In addition, one therapy session of each intervention group is videotaped and analysed for compliance with the manual by independent raters at the Frankfurt study centre. Reliability training in diagnostic measures has been performed before the start of the study.

As the proposed study is a behavioural therapy intervention study, blinding of participants as well as therapists or parents is not possible. Teachers are blinded to intervention. Therefore, a possible bias of the SRS-parent scores can be detected by comparing it to the SRS-teacher scores. The teacher scores, however, will not be used as primary outcome measure, as it is to be expected from previous studies [22] that return of teacher questionnaires will only be around 50 to 60%. Independent clinical on-site monitoring to ensure patient safety and integrity of the clinical data in adherence to the study protocol focuses on source data documentation, correctness of data, and adherence to trial procedures, for example, randomisation and treatment.

### Statistical analysis

Confirmatory analysis is performed for the ITT population, and is defined on the basis of the ITT principle. An additional per-protocol analysis will be conducted, which will include all patients without major protocol violations. Two primary endpoints are assessed in confirmatory analysis, namely the change in SRS total score between baseline and 12 weeks after baseline (effect at the end of therapy) and the change in SRS total score between baseline and three months after the end of therapy (maintenance effect). To ensure control of the multiple type I error rate at 5%, a hierarchical test procedure will be applied [23]: The first null hypothesis to be tested states that the change in SRS total score between baseline and 12 weeks after baseline is equal for both groups. If this hypothesis can be rejected at the two-sided significance level of 5%, the second null hypothesis stating that the change in SRS total score between baseline and three months after the intervention is equal in both groups is tested at the two-sided level 5%. If the first null hypothesis cannot be rejected, the second null hypothesis referring to the co-primary endpoint is also accepted.

Both null hypotheses will be tested by analysis of covariance with the covariates baseline SRS total score, age, IQ, and centre. Gender and medication effects were not observed in previous studies [14], and hence these variables are not included in the model of the primary analysis. Missing values with respect to post-baseline primary outcomes will be handled by application of the mixed-effects model for repeated measures (MMRM) approach that turned out to show favourable characteristics in terms of the type I error rate, power, and bias of estimates as compared to alternative methods dealing with missing values, such as last-observation-carried-forward (LOCF) [24-26].

Descriptive methods will be used for the analysis of the secondary outcomes, including calculation of appropriate summary measures of the empirical distribution as well as calculation of descriptive two-sided *P*-values. A special focus of the exploratory analysis will be with respect to the time course of the primary as well as the secondary endpoints. Additionally, sensitivity analyses will be conducted for different populations (per-protocol population, appropriate subgroups) and applying alternative imputation techniques (such as LOCF) for missing values. Further exploratory analyses will be performed to identify intervention effects in subgroups and potential prognostic factors (including genetic variants) for an intervention effect. Graphical methods will be applied to visualise the findings of the study. The safety analysis includes calculation and comparison of frequencies and rates of adverse and serious adverse events (SAEs) reported in the two intervention groups. All analyses will be done using the latest SAS version (9.1 or higher).

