## Methods/design

The SOSTA-net trial is designed as a prospective, randomised, controlled, multicentre trial, including an intervention and a waiting-list control group. The intervention includes 12 highly structured, manualised (SOSTA-FRA manual), weekly group-based social skills training, each of 90 minutes duration. Five children or adolescents take part in the intervention group, and the number of skilled behavioural therapists (that is, those who have studied at university for a minimum of 5 years and have undergone > 2 years of additional psychotherapy training) in each group is two (child-therapist ratio = 5:2). In addition, three parent training sessions are scheduled at the beginning, middle and end of the group therapy sessions, both for the intervention and the control group. The wait-list control group receives the same social skills training after the end of trial, that is, after 6 months (3 months intervention and 3 months follow-up).

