### Sample size calculation

The sample size calculation refers to the primary endpoint, change in SRS total score between baseline and 12 weeks after baseline, in the ITT population. The prior assumption for the treatment effect of the experimental intervention is based on the results of Tse *et al*. (2007) with a treatment mean difference of 11 points and SD of 28 points. It is assumed that the mean SRS total score does not change for the control group and that the same SD as in the experimental intervention holds true. With a two-sided significance level of α = 5% and a power of 1-β = 80%, a sample size of 206 (2 × 103) is required to detect this difference with a two-sample *t*-test. It can be expected that application of an analysis of covariance as defined for the evaluation (see below) will reduce the SD, thus increasing the actual power of the study. Based on the observations made in the study of Tse *et al*. (2007), the dropout rate during the intervention is assumed to be about 5%. Therefore, 220 individuals will be randomised in total, to obtain at least 206 evaluable patients. On the basis of the information from the clinical study centres, it is expected that about 25% of the screened patients cannot be included in the study due to violation of the inclusion/exclusion criteria. Hence, 300 patients will be assessed for eligibility. Sample size calculation was done using nQuery Advisor 7.0 [21].

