With regard to study methods, and similar to previous studies, parent rating (here: the parent- rated social responsiveness assessed by SRS) was chosen as the primary outcome measure. This is a critical aspect, as parents and their children cannot be blinded with regard to the intervention. Teachers are blind to the allocation of the ASD individuals to the intervention or control group. Thus, the present study also aims to obtain as many teacher-reported SRS data as possible. However, due to the well known difficulties in obtaining complete teacher ratings compared to parent ratings, the teacher-rated SRS was not chosen as a primary outcome measure. In addition to the primary outcome measure, several additional secondary outcome measures tapping ASD-specific behaviour and comorbid anxious and depressive symptoms, as well neural functional change induced by therapy, are clearly going beyond the currently published RCTs on SST in ASD. The automated online randomisation procedure is clearly defined and reflects the study design with respect to the multi-centre study and the group-based randomisation. The statistical analysis also takes the different study centres into account. A strong advantage of the current study is the 3 months follow-up assessment, providing some information on long-term effects of group-based SST in HFASD.

Finally, the therapeutic approach chosen, combining child-based SST with parent training to increase the children’s compliance with the training is a setting that can be easily implemented in non-university clinical settings. Compared with the published RCTs (Table 1), therapeutic frequency is fairly similar with 12-weekly sessions of 90 minutes of SST. The only exception to the weekly training sessions was in the very intensive summer camp treatment program by Lopata *et al*. (2010), which provides many more therapy hours, but might be less cost-effective compared to weekly SST programs that can also be provided throughout the year. In addition to the traditional SST in ASD focusing on social rule-based learning, social understanding and practising of social skills, the SOSTA-FRA manual also includes executive function training, anger control strategies, and training of behavioural and cognitive flexibility overcoming stereotyped behaviour and intense special interests interfering with social interaction. Thereby, it addresses the broad range of everyday difficulties in children and adolescents with ASD.

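### Social skills training is delivered in groups of five, but the confirmatory model and the sample size have no therapy-group term; any positive within-group correlation pushes the type I error above 5% and makes the stated 80% power conditional

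*Protocol article*

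**What the plan says.** Delivery is by group. Methods/design states "Five children or adolescents take part in the intervention group", with two therapists per group; the Intervention section repeats the two therapists, and the Assessment section speaks of at least five children per first session. The Assessment section also says that ten children of similar age form a cohort and are then randomised. Under Methods against bias, allocation is 1:1 and stratified by centre.

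The sample size section uses "a treatment mean difference of 11 points and SD of 28 points", assumes that "the mean SRS total score does not change for the control group" and that both arms have the same SD, and concludes that "a sample size of 206 (2 × 103) is required to detect this difference" with a two-sample t-test at two-sided 5% and 80% power. It gives no ICC and no design effect. It adds, without a figure, that analysis of covariance should reduce the SD and raise the actual power.

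For the analysis: "Both null hypotheses will be tested by analysis of covariance with the covariates baseline SRS total score, age, IQ, and centre". A mixed model for repeated measures (MMRM) is named for missing post-baseline values, and a hierarchical procedure is said to hold the multiple type I error at 5%. The Discussion adds: "The statistical analysis also takes the different study centres into account". No therapy-group or therapist term appears anywhere.

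**The concern.** The training consists of peer interaction under shared therapists, and the withdrawal criteria recognise that one child's behaviour can be directed against others in the group. Outcomes of children in one group may therefore be correlated, in the intervention arm only. This is a partially nested design: about 110/5 = 22 treated groups against individually followed controls.

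The two structures in the planned model do not cover this level. Centre absorbs differences between six sites, not between groups within a site that exist in one arm only. The MMRM covariance links the repeated scores of one child, not the scores of different children.

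If the correlation is positive, the standard error of the treatment difference is too small. That affects both confirmatory hypotheses, because the second is tested with the same model once the first is rejected. At stake are the claimed 5% error control and the coverage of the intervals, and also the basis of the 80% power figure.

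**Working it through.** **Inputs.** From the sample size section: difference 11, SD 28, two-sided 5%, 103 per arm. From Methods/design: group size m = 5. Assumed, because the documents give none: ICC ρ from 0.01 to 0.20, where ρ is the correlation created by the training group itself.

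**1. The plan's own figure.** The standard error of the difference is 28 × √(2/103) = 3.90, so the noncentrality is 11/3.90 = 2.82. The noncentral t distribution gives power 79.7% at 102 per arm and 80.1% at 103. The stated 206 reproduces, under independence (ρ = 0).

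**2. Effect of the groups.** The variance of the treated-arm mean is multiplied by 1 + (m − 1)ρ = 1 + 4ρ and that of the control mean by 1. With equal arms, the variance of the difference is multiplied by V = [(1 + 4ρ) + 1]/2 = 1 + 2ρ.

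**3. Formulas.**
- Type I error of the planned test, which ignores groups: 2 × [1 − Φ(1.96/√V)].
- Power of a test that accounts for groups: noncentral t with noncentrality 2.82/√V.
- Power of the planned test (normal approximation): Φ((2.82 − 1.96)/√V).
- Share of variance that covariates must explain to cancel V: 1 − 1/V.

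| ρ | V | Type I error, planned test | Power, group-adjusted test | Power, planned test at its inflated error rate | Variance share to offset |
|---|---|---|---|---|---|
| 0 | 1.00 | 5.0% | 80.1% | 80.5% | 0% |
| 0.01 | 1.02 | 5.2% | 79.3% | 80.3% | 2% |
| 0.02 | 1.04 | 5.5% | 78.6% | 80.0% | 4% |
| 0.05 | 1.10 | 6.2% | 76.3% | 79.4% | 9% |
| 0.10 | 1.20 | 7.4% | 72.6% | 78.4% | 17% |
| 0.20 | 1.40 | 9.8% | 66.0% | 76.6% | 29% |

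Both power columns are before any covariate gain. The group-adjusted column uses 204 degrees of freedom; a small-sample correction based on about 22 groups would lower it slightly.

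**4. Simulation check.** An analysis of covariance with centre and no group term was simulated with 21 cohorts of five treated and five control children, six centres and 6,000 runs. It gave a type I error of 4.8%, 5.4%, 5.7%, 7.5% and 9.3% at ρ = 0, 0.02, 0.05, 0.10 and 0.20. This agrees with the formula to within about half a percentage point.

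**5. Similarity shared by a ten-child cohort.** A cohort component common to both arms (5% of the variance) was added to the simulation. The type I error was then 4.7%, 4.4%, 5.9%, 6.8% and 9.3% at the same values of ρ, so this component did not add to the inflation. It balances across arms. Only correlation specific to the training group counts.

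**The case against.** **The size is unknown.** No ICC is given, and at 0.01 to 0.02 the effect is small (5.2% to 5.5%). Ratings come from each child's own caretaker, and delivery is manualised with training, supervision and video checks, which should limit variation between groups. This stands. A reader might infer that the 5% level and the 80% power are simply not achieved; the documents do not support that, because both statements depend on an ICC they do not contain.

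**The power loss may not occur.** A reader might take 76%, 73% and 66% as the power of the planned test. They belong to a test that accounts for the groups and has no covariate gain. The planned test keeps about 79%, 78% and 77% at ICC 0.05, 0.10 and 0.20, at an inflated error rate. Inflated error and lost power are therefore not joint harms of one test. The covariate gain that the article expects could also make up the loss. This stands, but covariates measured at baseline do not remove correlation that arises during group treatment.

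**No effect, no clustering.** If the training changed nothing for any child, no group component would arise. True, but the hypothesis tested is equality of mean change. Group-specific effects that average to zero satisfy it and still inflate the error, and interval coverage suffers whether or not the null holds.

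**Random effects belong in the analysis plan.** That plan is not shown and may contain one. However, the article states the confirmatory model with its covariates, explains why gender and medication are left out, names the higher level it covers (centre) and claims 5% control. That is a stated choice, not a detail left open.

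**Larger clusters.** A reader might infer still greater inflation from therapists leading several groups, or from clustering in the control arm through its parent sessions. The number of therapists is not given, and it is not stated whether control parents meet in fixed groups. Neither is part of the conclusion.

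**Conclusion.** The point holds in conditional form. For any positive correlation specific to the training groups, the stated model understates the standard error for both confirmatory hypotheses. With groups of five in one arm and an assumed ICC of 0.01 to 0.20, the type I error is about 5.2% to 9.8%, and the true standard error is √V = 1.01 to 1.18 times the one the model reports. This is the robust part, because nothing in the planned model corrects it.

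The power part is weaker. The 206 children give 80% only at an ICC of zero on the article's t-test inputs. Whether a valid test falls short depends on the ICC and on how much variance the covariates explain, and the article gives neither figure.

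**What to change.** 1. Add a random effect for therapy group in the intervention arm to the confirmatory model at both time points, with each control child as its own cluster (a partially nested mixed model). Use Kenward-Roger or Satterthwaite degrees of freedom. If the analysis plan already does this, the article's description of the model should say so.
2. Report the estimated ICC with the primary result.
3. Restate the power as conditional on an assumed ICC range and on an explicit variance reduction from the covariates, in place of a flat 80%.

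The first item matters most. According to Trial status, 204 of the planned 220 children were already randomised in October 2012, so the model is what can still be changed. The work is a change of wording and one extra model term; group membership should be known from delivery. No extra patients are needed. The price is slightly wider intervals and a less favourable stated power.

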### Safety aspects

An independent Data and Safety Monitoring Board (DSMB) is established, involving two independent clinical experts and one biometrician for monitoring the progress of the trial and ensure adherence to protocol. Safety parameters are all SAEs and adverse events (AEs) reported by the subject or PC, or detected by the local investigator, that occur during and up to three months after treatment. All noticeable problems must be documented in the CRF. Even though the character of the intervention as a behavioural therapy makes SAEs extremely unlikely, the Ethics Committee and DSMB will be informed in the case of SAEs within 24 hours after the SAE becomes known.

### Ethical issues

The procedures set out in the trial protocol pertaining to conduct, evaluation and documentation of this trial is designed to ensure that all persons involved in the trial comply with Good Clinical Practice (GCP) and the ethical principles described in the latest accepted version of the Declaration of Helsinki in Germany. The trial is carried out in keeping with local legal and regulatory requirements, although German Drug Law (AMG) and Medical Device Law (MPG) are not applicable. Each site’s principal investigator ensures that all persons assisting with the trial are adequately informed about the protocol, any amendments to the protocol, the trial treatments, and their trial-related duties and functions. Before the first subject has been enrolled, all ethical and legal requirements have been met. Study protocol, patient information and the respective consent form were approved by the responsible Ethical Committees before the start of the trial. The study protocol was first ethically reviewed by the ethical committee of the Medical Faculty, Goethe Universität, Frankfurt am Main, Germany, on 30 March 2010 (No. 57/10). Subsequent approval of this vote was done by the ethical committees of the Medical Faculties in Aachen (27 August 2010), Köln (1 September 2010), Mannheim (7 September 2010), Würzburg (25 October 2010), and the Ärztekammer des Saarlandes, Germany (26 May 2010). Parents and participants are informed individually about the study and need to consent separately to the three parts of the study (intervention, genetics, and neurophysiology). Participants are allowed to take part only in the intervention study if they do not agree to the genetic or neurophysiological part of the study. Throughout the trial, subjects are pseudonymised. Authorized persons (clinical monitors) regularly control adherence to protocol. During on-site visits, they inspect subject-related data to ensure adherence to data protection laws and correctness and completeness of data. As TAU is allowed for the treatment and the control group, and as the control group can take part in the training after completion of the trial, the treatment and control group experience no disadvantage related to clinical intervention by taking part in the trial.

## Discussion

This study is currently one of the largest trials worldwide on SST in children and adolescents with HFASD. When the study was planned in 2008, no RCTs on SST in HFASD had been published in an English, or German, scientific peer-reviewed journal. Since then, the studies shown in Table 1 have been published. Compared to these studies, our study shows several advantages with regard to the following aspects: (1) sample with specific inclusion and exclusion criteria; (2) study methods; and (3) therapeutic approach.

With regard to the ASD sample, not only the diagnostic criteria for ASD are obtained by standardised instruments, but also an additional standardised diagnostic interview is performed to assess psychiatric comorbid disorders in the study participants. Only psychiatric disorders that necessitate a different kind of therapeutic management are excluded as comorbid disorders. This reflects the current epidemiological findings on the high rate of psychiatric comorbid disorders in ASD [4], and allows secondary analyses on the kind and rate of comorbid psychiatric disorders and their influence on therapeutic outcome. Going beyond previous RCTs, not only children but also adolescents are included, and the study manual provides specific age-appropriate training material. Also, children with IQ >= 70 (compared to IQ > 85) are allowed into the trial, which reflects the clinical need of many children with ASD. These inclusion criteria are rather broad and may result in a somewhat smaller effect size of the intervention in the full group compared to the recently published trials, but also will allow probing for factors influencing therapy outcome. Similarly, stable medication is allowed in this trial, reflecting clinical practices, and again allowing testing of the influence of the combined treatment on outcome in secondary analyses.

With regard to study methods, and similar to previous studies, parent rating (here: the parent- rated social responsiveness assessed by SRS) was chosen as the primary outcome measure. This is a critical aspect, as parents and their children cannot be blinded with regard to the intervention. Teachers are blind to the allocation of the ASD individuals to the intervention or control group. Thus, the present study also aims to obtain as many teacher-reported SRS data as possible. However, due to the well known difficulties in obtaining complete teacher ratings compared to parent ratings, the teacher-rated SRS was not chosen as a primary outcome measure. In addition to the primary outcome measure, several additional secondary outcome measures tapping ASD-specific behaviour and comorbid anxious and depressive symptoms, as well neural functional change induced by therapy, are clearly going beyond the currently published RCTs on SST in ASD. The automated online randomisation procedure is clearly defined and reflects the study design with respect to the multi-centre study and the group-based randomisation. The statistical analysis also takes the different study centres into account. A strong advantage of the current study is the 3 months follow-up assessment, providing some information on long-term effects of group-based SST in HFASD.

Finally, the therapeutic approach chosen, combining child-based SST with parent training to increase the children’s compliance with the training is a setting that can be easily implemented in non-university clinical settings. Compared with the published RCTs (Table 1), therapeutic frequency is fairly similar with 12-weekly sessions of 90 minutes of SST. The only exception to the weekly training sessions was in the very intensive summer camp treatment program by Lopata *et al*. (2010), which provides many more therapy hours, but might be less cost-effective compared to weekly SST programs that can also be provided throughout the year. In addition to the traditional SST in ASD focusing on social rule-based learning, social understanding and practising of social skills, the SOSTA-FRA manual also includes executive function training, anger control strategies, and training of behavioural and cognitive flexibility overcoming stereotyped behaviour and intense special interests interfering with social interaction. Thereby, it addresses the broad range of everyday difficulties in children and adolescents with ASD.

In conclusion, this large multi-centre RCT on the manualised SOSTA-FRA program addresses a strong clinical need and will provide further insight into the efficacy of SST, its moderating factors, and the 3-month long-term effects of SST in individuals with HFASD.

